Participants are considered withdrawn from the study if any of the following occurs: (1) voluntary withdrawal at any time without the need to provide a reason; (2) emergence of adverse effects or discomfort judged to make continuation inappropriate; (3) detection of a major protocol deviation; or (4) any circumstance that, in the investigators’ clinical judgment, could compromise the participant’s health safety, or well-being. The date and reason for withdrawal will be systematically recorded in a paper-based case report form (CRF).

Recruitment is anticipated to be completed by December 2026.

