### Interventions

#### Participants

Participants in the control group do not receive VR training but follow the same assessment schedule as the experimental group. Specifically, they complete baseline (T0), post-intervention (T1), and follow-up (T2) evaluations using the same psychological measures. This design allows comparison between intervention and control conditions, thereby isolating the effects of VR training from potential confounding factors such as time and repeated testing effects.

The experimental intervention includes two distinct VR-based training components: (A) VR-ERP, which gradually exposes students to anxiety-provoking situations to prevent avoidance responses, and (B) VR-ACT training, which provides consistent mindfulness practice aimed at enhancing psychological flexibility and value-oriented behaviors. After completing VR-ACT training, participants in the experimental group proceed to a standard counseling intervention.

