### Statistical analyses

All statistical analyses are conducted using IBM SPSS Statistics (version 29.0) and follow a pre-specified analytic strategy designed to evaluate changes in psychological and physiological outcomes across the study period and to compare the effectiveness of standard counseling with and without VR-based exposure. Descriptive statistics are first computed to characterize the sample to assess baseline equivalence between groups. Reliability analyses (Cronbach’s α and McDonald’s ω) are performed to confirm the internal consistency of the psychometric instruments.

Because the study involves repeated assessments at baseline (T0), post-intervention (T1), and follow-up (T2), the primary analyses use linear mixed-effects models, an approach well suited to handling longitudinal data and missing observations. These models test for the main effects of time and group, as well as the critical time × group interaction, indicating differential improvement between the VR-enhanced counseling condition and the control group. Where significant interactions emerge, post hoc comparisons with Bonferroni adjustment are conducted to identify specific temporal patterns of change. Complementary analyses of change scores (ΔT1–T0 and ΔT2–T0) are performed using independent-sample t-tests or, where assumptions are violated, Mann–Whitney U tests; General Linear Models including baseline variables and demographic covariates further clarify group differences in treatment response.

Physiological data collected during VR sessions (including heart rate, HRV, and electrodermal activity) are examined through mixed models and event-based analyses aligned with the structure of the VR exposure tasks, allowing evaluation of both arousal patterns and recovery processes. Exploratory regression models are used to identify predictors of treatment benefit, such as baseline symptom severity or physiological reactivity during VR exposure.

Missing data are handled through the mixed-model framework, which accommodates incomplete longitudinal data; if dropout shows non-random patterns, multiple imputation is applied as a sensitivity check. For all analyses, statistical significance is set at α = 0.05, with appropriate corrections for multiple comparisons.

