This study has the potential to help address factors associated with university dropout rates linked to anxiety, contribute to improvements in overall psychological well-being among university students, and offer an accessible, and potentially cost-effective alternative to traditional psychotherapy. Additionally, the project strengthens interdisciplinary collaboration between psychology, engineering, and computer science students, fostering professional competencies in digital mental health design.

Some potential limitations and practical challenges may arise during the implementation of this study. One limitation of this study is its requirement for high participant commitment, which may have reduced engagement and increased attrition, thereby limiting the generalizability of the findings. Another limitation concerns the sample composition, as the study focuses on help-seeking university students, a group that may differ in motivation, access to technology, and psychological awareness compared to the general population or younger adolescents. This restricts the ability to generalize the results to other demographic or clinical groups. Finally, the relatively short follow-up period restricts conclusions regarding the long-term maintenance and generalization of treatment gains to real-world academic performance contexts.

Despite these constraints, the study is expected to provide valuable preliminary evidence regarding the feasibility, acceptability, and potential efficacy of VR-based interventions for anxiety management within higher education. The results will help inform the design of larger randomized controlled trials and support the development of scalable, evidence-based digital interventions that integrate VR with established therapeutic approaches, with the aim of enhancing accessibility, engagement, and personalization in mental health care.

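### The withdrawal rule merges stopping the intervention with leaving the study, which risks arm-dependent, outcome-related loss of T1 and T2 data

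*Protocol article*

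**What the plan says.** The rule stands at the end of Participants and recruitment in the protocol article. It opens: "Participants are considered withdrawn from the study if any of the following occurs". Four triggers follow. The first is the participant's own choice. The second and third are "2) emergence of adverse effects or discomfort judged to make continuation inappropriate; (3) detection of a major protocol deviation". The fourth is "any circumstance that, in the investigators’ clinical judgment, could compromise the participant’s health safety, or well-being". The status in every case is withdrawal from the study. No separate status exists for a student who stops VR or counseling but could still fill in questionnaires. What is kept on such a student is described in one sentence, which begins: "The date and reason for withdrawal will be systematically recorded in a paper-based case report form (CRF".

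The arms differ in what can trigger the rule. Under Interventions, Participants: "Participants in the control group do not receive VR training but follow the same assessment schedule as the experimental group".

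On analysis, the section Statistical analyses says that "the primary analyses use linear mixed-effects models, an approach well suited to handling longitudinal data and missing observations". It adds that "if dropout shows non-random patterns, multiple imputation is applied as a sensitivity check". Change from T0 to T1 and from T0 to T2 is also compared by t-test or Mann–Whitney test.

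**The concern.** The stated aim is to learn whether adding VR to routine counseling gives benefit beyond counseling alone. That question needs outcomes on everyone allocated, including students who stop early or depart from the protocol. A rule that turns a deviation or discomfort into study withdrawal discards outcomes for reasons that arise after randomisation and are tied to the treatment received.

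Two features make the loss potentially uneven and informative. First, headset discomfort and departures from the VR-ERP or VR-ACT modules can arise only in the experimental arm. Second, the VR-ERP scenes are designed to provoke anxiety, so discomfort in them lies close to what PRPSA and STAI measure. A link between withdrawal and poor outcome is therefore plausible, though the documents do not establish one.

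The third trigger is the hardest to justify as a reason to leave the study. Safety has its own trigger, the fourth. A protocol deviation by itself is no reason to stop asking a student for a questionnaire.

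This is also not a matter that a separate analysis plan could settle later. Such a plan can define who is analysed, but it cannot recover T1 and T2 scores that were never collected.

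**Working it through.** **1. The plan's own figure.** Inputs from Sample size: d = 0.75, two-sided α = 0.05, power 0.80, 1:1 allocation, 20% dropout. The two-sample t-test (noncentral t) gives n = 28.90, so 29 per group with power 0.801. This agrees with the plan. For dropout, 29 / 0.8 = 36.25. The plan takes 36 per group, and 36 × 0.8 = 28.8 completers gives power 0.799. The sample size is not affected by this point. The 20% is one overall allowance, not split by arm or reason. It protects precision and does nothing against bias.

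**2. What the primary model does with a withdrawn student.** A student withdrawn before T1 contributes only T0, which adds almost nothing to the T1 contrast. In effect the model gives that student the response of the retained students in the same arm, given baseline. That is correct under missing at random. It is not correct if discomfort or non-adherence carries information on T1 beyond what was observed. Standard multiple imputation makes the same assumption, so it does not test it.

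**3. Possible size.** The documents give neither a withdrawal rate by arm nor a link to outcome, so both are assumed here. Assumptions:
- withdrawal occurs in the VR arm only, in a fraction w;
- the T1 change is normal with SD 1;
- a normal withdrawal propensity has correlation r with poor outcome;
- the analysis uses observed data, as the planned change-score t-test does.

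Bias in favour of VR = r × φ(z) / (1 − w), with z = Φ⁻¹(1 − w).

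- w = 0.05: φ(1.645) / 0.95 = 0.1031 / 0.95 = 0.109
- w = 0.10: φ(1.282) / 0.90 = 0.1755 / 0.90 = 0.195
- w = 0.20: φ(0.842) / 0.80 = 0.2800 / 0.80 = 0.350

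Multiplying by r gives the bias in SD units:

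| r | w = 5% | w = 10% | w = 20% |
|---|---|---|---|
| 0 | 0 | 0 | 0 |
| 0.3 | 0.033 | 0.058 | 0.105 |
| 0.5 | 0.054 | 0.097 | 0.175 |
| 1 (extreme) | 0.109 | 0.195 | 0.350 |

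Set against the planned d = 0.75, the range for r = 0.3–0.5 and w = 10–20% runs from 0.058 / 0.75 = 8% to 0.175 / 0.75 = 23%.

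**4. Effect on the test.** Simulated two-sided type I error of the t-test on T1 change, 36 randomised per arm, no true effect, nominal 0.05, 4,000 runs:

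| r | w = 10% | w = 20% |
|---|---|---|
| 0 | 0.047 | 0.053 |
| 0.3 | 0.056 | 0.068 |
| 0.5 | 0.075 | 0.103 |
| 1 (extreme) | 0.168 | 0.300 |

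The simulation error near 0.05 is √(0.05 × 0.95 / 4000) = 0.003. The value 0.056 is therefore not clearly above nominal, while 0.068 and the higher values are.

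**The case against.** Several points on the other side are fair.

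- **Loss of T1 and T2 is inferred.** The text says neither that questionnaires stop at withdrawal nor that collected data are deleted. This stands as a caveat. Even so, loss is the natural reading of withdrawal from the study when only a date and a reason are said to be recorded.
- **The rule is not written against VR or against poor responders.** A reader might infer that it removes students who do badly on VR. The documents do not support that. The trigger is discomfort in general, the schedule in Table 1 does not limit adverse events or discomfort to one arm, and poor response is not a trigger. Control students can also deviate, for example by missing sessions. VR adds one source of events in one arm. The net imbalance and its direction are not fixed.
- **The plan recognises non-random dropout.** It offers multiple imputation as a check. This deserves credit, but the check is conditional and in its standard form shares the model's assumption.
- **No statement on analysing all randomised participants as allocated.** A reader might count this as a defect. It is not one here, because a condensed article commonly leaves analysis sets to the full protocol or analysis plan.
- **A larger fixed overstatement.** One might suppose that 10% or 20% of the VR arm is withdrawn by this rule with no gain at all from VR. The all-randomised effect is then 0.75 × 0.90 = 0.675 or 0.75 × 0.80 = 0.60, and a reported 0.75 overstates it by 11% or 25%. That is a constructed case. It attributes the whole dropout allowance to these triggers although voluntary withdrawal falls within it, assumes zero benefit after partial exposure, treats 0.75 as the effect in completers, and allows no loss among controls.

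**Conclusion.** The point holds as a risk that the wording creates, not as a demonstrated bias. The article states a positive rule that makes discomfort or a major protocol deviation grounds for leaving the study. Followed as written, it is likely to cost T1 and T2 outcomes for reasons connected with treatment received, and one source of such events exists in the VR arm only. The planned mixed model and imputation would not remove the part of that loss that is not at random.

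The size is unknown. With withdrawal in the VR arm only, at 10–20%, the bias in an observed-data T1 comparison is 0 if withdrawal is unrelated to outcome and about 0.06–0.18 SD if its correlation with poor outcome is 0.3–0.5. Losses in the control arm could reduce or offset this. A reader might conclude that the comparison is certain to be biased in favour of VR. The documents do not support that, since they fix neither the rates nor the link to outcome. The change is nevertheless worth making, because outcomes not collected cannot be recovered at analysis.

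**What to change.** In Participants and recruitment:

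1. Define two separate events: discontinued intervention, and withdrew from follow-up.
2. Remove major protocol deviation as a reason for study withdrawal, and record it as a deviation.
3. State that T1 and T2 questionnaires are collected from every randomised participant unless the participant refuses, and that all of them stay in the primary mixed model in the arm to which they were allocated.

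This concerns data collection and analysis only. Who should stop VR or counseling, and when, remains the clinicians' decision and is unaffected.

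The cost is small: protocol wording, one additional CRF field, and a few self-report questionnaires. One practical step is needed. The counseling program section has T1 administered in session five, so students who stop earlier need a separate contact to obtain it. Recruitment is expected to run until December 2026. The sooner the wording changes, the fewer students are handled under the present rule.

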### Ethics and privacy

Written informed consent will be obtained from participants prior to study participation, following a comprehensive explanation of the study aims, procedures, and the provision of written information. The study received ethical approval (No. 112518/2025) from the Institutional Review Board Committee (IRBC) of the University of Calabria and is registered with the ClinicalTrials.gov (NCT07351409) on January 16, 2026. Data will be collected through a secure, encrypted digital platform and stored on institutional servers in compliance with General Data Protection Regulation (GDPR) and institutional ethics guidelines. All datasets used for analysis will be fully de-identified using unique participant identification codes.

### Assessment instruments

Participants complete a self-administered questionnaire to collect sociodemographic and academic data, including gender, age, degree programme, and disciplinary area (e.g., STEM, humanities, social sciences), year of study, and enrollment status (in-course/out-of-course).

#### Psychological assessment

The protocol involves the assessment of participants through the administration of standardized self-report psychological tests designed to evaluate levels of public speaking anxiety and state and trait anxiety levels.

The instruments are:

The Italian version of the *Personal Report of Public Speaking Anxiety* (PRPSA) [23] is a self-report questionnaire designed to measure the level of anxiety individuals experience when speaking in public. The scale assesses multiple dimensions of public speaking anxiety, including cognitive, physiological, and behavioral components, capturing both anticipatory anxiety and anxiety during performance. The PRPSA consists of 34 items, each rated on a 5-point Likert scale (1 = strongly disagree to 5 = strongly agree). Items reflect feelings of tension, nervousness, and physiological arousal (e.g., “My hands tremble when I try to handle objects on the podium”), as well as negative self-appraisal and fear of audience evaluation. Total scores range from 34 to 170, with higher scores indicating greater levels of public speaking anxiety. Conventionally, scores above 131 suggest high anxiety, scores between 98 and 131 indicate moderate anxiety, and scores below 98 indicate low anxiety. The Italian version maintains strong psychometric properties, with high internal consistency (Cronbach’s α > 0.90) and good test–retest reliability. It has been validated for use among university students and adults, proving useful in both clinical and research contexts, examining performance-related social anxiety and communication apprehension.The Italian version of the *State-Trait Anxiety Inventory*,* Form Y* (STAI) [24, 25] was adopted to measure two distinct dimensions of anxiety: (i) State Anxiety (S-Anxiety), a temporary emotional condition characterized by feelings of tension, apprehension, and heightened autonomic nervous system activity, reflecting how the respondent feels at the present moment; and (ii) Trait Anxiety (T-Anxiety), a relatively stable disposition to perceive situations as threatening and to respond with anxiety across time and contexts. Each subscale consists of 20 items, rated on a 4-point Likert scale (ranging from 1 = almost never to 4 = almost always for trait anxiety, and 1 = not at all to 4 = very much so for state anxiety). Scores range from 20 to 80 for each subscale, with higher scores indicating greater anxiety levels. The Italian adaptation has demonstrated good psychometric properties, including high internal consistency (Cronbach’s α typically between 0.86 and 0.95) and construct validity consistent with the original instrument, making it one of the most widely used anxiety measures in both clinical and research settings in Italy.

The psychological tests used to assess the students will be administered at baseline (T0), post-treatment (T1, at the end of the 4-week intervention period), and after 3 months (T2, follow-up).

#### Physiological assessment

The EmbracePlus wristband is a research-grade, wrist-worn wearable device designed to continuously monitor a range of physiological parameters, providing real-time access to raw sensor data suited for scientific, clinical, and real-world studies. Its built-in sensors include photoplethysmography (PPG) for blood volume pulse (BVP), from which heart rate (HR), inter-beat interval (IBI), and heart rate variability (HRV) are derived, electrodermal activity (EDA or skin conductance) as an index of autonomic arousal, a 3-axis accelerometer to track motion and activity, and a peripheral skin-temperature sensor. The device samples EDA at 4 Hz and PPG at 64 Hz, and it has demonstrated high correlations with clinical-grade equipment for HR and HRV under controlled conditions (though less so for EDA under movement) [26]. Thanks to its wrist-worn design, on-board data storage, and Bluetooth syncing capabilities, the EmbracePlus enables extended ambulatory monitoring of physiological responses in naturalistic settings, enabling studies of stress, emotion, cognitive load, and behavioral states in real time. Data were collected during four intervention sessions, from Session 1 (T0; baseline) to Session 4 (T1), corresponding to the end of the 4-week intervention period.

### VR materials

A custom VR application was developed using Unity (version 2023) and deployed on the Meta Quest 3 head-mounted display (HMD). The Quest 3 is a fully standalone and wireless HMD, allowing participants to move freely without being physically tethered to an external computer. The system provides full visual isolation from the real-world environment and delivers a highly immersive first-person experience.

Participants are placed in a realistically reconstructed academic setting, which includes either a virtual classroom or a lecture theatre, where they are positioned in front of a virtual professor or an examination committee and an audience of virtual observers. Participants are required to engage in a structured oral examination or public speaking task. The primary goal of the system is to induce and study public speaking anxiety under controlled, ecologically valid experimental conditions.

The virtual professor and audience are animated and temporally synchronized with audio output to enhance perceived realism and social presence. The system ensures consistent experimental conditions across participants while allowing controlled variation of environmental and social parameters.

For safety and ethical compliance, participants can immediately terminate the VR session at any time by simply removing the headset, which instantly ends the immersive experience. To ensure high experimental control and to prevent simulator-induced artifacts that could confound psychological and physiological measurements, the VR application was optimized to maintain a stable high refresh rate under all experimental conditions. In particular, the system was designed to support parametrically variable audience sizes without performance degradation, as audience size represents a key experimental stressor [27]. To meet these constraints, the rendering pipeline was implemented using GPU instancing for efficient large-scale replication of audience avatars and GPU-based animation techniques to offload character animation from the CPU [28]. This architecture enables real-time scalability of animated virtual agents while preserving consistent frame timing and minimizing motion-to-photon latency. These optimizations ensure that observed variations in biometric and physiological responses can be attributed to experimental manipulations rather than to technical artifacts such as frame drops, stuttering, or rendering instability.

A dedicated PC-based control software application, developed using Microsoft Visual Studio, allows the experimenter to monitor, manage, and customize the VR session in real time. Through this interface, the experimenter can configure multiple key experimental parameters, including:

the type of virtual environment (e.g., classroom or lecture theatre);the number of virtual audience members;the general structure and difficulty of the speaking or examination task.

The control software communicates bidirectionally in real time with the VR application, enabling the dynamic delivery and modulation of stimuli, questions, and scenario changes during the session. All experimental parameters are automatically time-stamped and logged for subsequent analysis. The control software integrates with OpenAI’s language model through an Application Programming Interface (API), enabling the dynamic and personalized generation of examination questions. The experimenter can enter high-level natural language prompts describing the participant’s academic background (e.g., *“Ask the student about a second-year engineering class”*). The language model then generates a contextually appropriate academic question, which is transmitted in real time to the VR application and delivered verbally by the virtual professor to the participant. This approach enables:

high variability and adaptability of task content;personalization based on participant characteristics and academic context;increased ecological validity of the simulated social interaction.

All input prompts and corresponding AI-generated examination questions are automatically stored and time-stamped in the system log for later quantitative and qualitative analyses.

During each VR session, participants wear a medical-grade wrist-worn biometric device (EmbracePlus), part of the Empatica Health Monitoring Platform. The system continuously records multiple physiological parameters associated with stress and emotional arousal, including:

heart rate (HR);heart rate variability (HRV);electrodermal activity (EDA);skin temperature;movement and activity levels.

The biometric device operates independently from the VR system but is time-synchronized with the experimental software, ensuring precise temporal alignment between physiological signals and VR events. Both the VR application and the PC-based control software automatically generate detailed time-stamped log files, including:

environment configuration parameters;audience size and room type;All AI-generated questions are delivered to the participant;session start and end times;user interaction events within the VR environment.

After each session, biometric data collected from the Empatica platform and behavioral and system-level data from the experimental software are exported and temporally aligned using synchronized timestamps. This enables precise mapping between physiological responses and specific experimental events (e.g., question onset, manipulation of audience size), allowing the identification of biometric markers associated with public speaking anxiety and stress responses. An overview of the system architecture is presented in Fig. 1.

